## Abstract

Background and objectives: *Clostridium difficile* infections (CDI) among elderly individuals are common. Antibiotic use and gut dysbiosis are major contributors to CDI. Probiotics and prebiotics help prevent CDI by addressing dysbiosis. This study aims to document the effect of the combination of probiotics from *Torani*, a traditional fermented food (rich in *Lactobacillus* species), and prebiotics (xylitol) on CDI among elderly hospitalized individuals.

Methods: This two-arm, open-label, randomized controlled trial (RCT) will be conducted at a tertiary care hospital in Odisha, India. The eligible elderly hospitalized participants will be randomized into two groups in a 1:1 ratio to receive 350 ml of either *Torani*-xylitol mixture or plain water once daily for 14 days. The data on sociodemography, clinical, and laboratory tests, antibiotics, and other medications used shall be recorded from their case sheets. Stool samples or rectal swabs will be collected on days 0 and 15 or at discharge/death/referral for CD isolation. A stool or rectal swab sample will be collected for any suspected CDI during the hospitalization. Follow-up contacts will be made on days 30 (+7), 60 (+7), and 90 (+7) to address any illness/infection, medication use, hospitalization, blood tests, and dietary practices.

Results: As we have not started the study, we do not have any observations yet.

Conclusions: This RCT shall document the effect of *the Torani*-xylitol mixture on CDI prevention and CD colonization among hospitalized elderly individuals. If found effective, it can promote using beneficial fermented foods to prevent CDI, reducing morbidity, mortality, hospitalization rate, and duration, cost of therapy, and bed occupancy.

## Introduction

*Clostridioides difficile* (also known as *Clostridium difficile*) infections (CDI) are linked to extended hospital stays and fatalities, particularly in the elderly population [1]. Though CDI is considered a nosocomial infection, community-based transmission among older adults is common [2]. An increase in CDI incidence has been observed in American, European, and certain Asian hospitals over time. This tendency can be attributed to the increasing antibiotic usage and the emergence of novel, hypervirulent strains [3-6]. In parallel with the rising CDI incidence, the antibiotic resistance pattern and associated mortality have also increased [7].

*Clostridioides difficile* (CD) usually spreads by the fecal-oral route and causes exotoxin-mediated illness. In India, CDI affects 3.4-18% of people, with older adults having a greater risk [8]. While 3-15% of healthy persons may have CD in their normal flora, 16-35% of hospitalized patients may have asymptomatic colonization [9,10]. The most significant risk factor for CDI is the use of antibiotics. The antibiotic class and its exposure duration determine the infection likelihood [11].

The resistance of the bacterial spores to heat and disinfectants contributes to the spread of CDI in hospitals. CDI ranges from mild diarrheal symptoms to fatal colitis [3,12]. Nowadays, community-acquired colitis is more prevalent owing to CDI and infective diarrhea [12]. Recurrent CDI (rCDI) increases morbidity, mortality, and healthcare costs and dampens the quality of life [3,12,13]. A recent meta-analysis shows 8.3 CDI cases for every 10,000 patient days [13]. Complex carbohydrate conversion by the normal colonic microbiota is essential to elicit resistance to invading microorganisms [14]. Gut microbiomes digest complex carbohydrates, starch, and dietary fiber to create short-chain fatty acids (SCFAs). SCFAs modulate inflammation and the immune system by lowering T and B cell differentiation and migrating immune cells (i.e., neutrophils, dendritic cells, and macrophages) [15].

Gut dysbiosis leads to acidification of the pH of the large intestine and, thereby, CD colonization and CDI [16]. Probiotics, prebiotics, and fecal microbiota transplantation have reduced CDI and CD colonization [17]. However, studies evaluating the additional benefits of SCFAs are scarce. Unlike probiotics and prebiotics, SCFAs are not easily available in the market. Xylitol, a transparent polyol, is a good substrate for SCFAs in the large intestine [18]. Various types of SCFAs, minerals, micronutrients, and commensal gut microbiota are abundant in fermented foods. Thus, they can positively impact immunomodulation, inflammation control, and gut microbiota regulation [19]. In India, many traditional fermented foods are consumed in households. These foods' cost, ease of administration, and sociocultural preparation render them good options for maintaining colonic ecology.

In the Indian state of Odisha, traditional fermented food includes Pakhala bhat (fermented rice) and *Torani* (fermented rice-water). In the *Torani*, the complex carbohydrates of rice are broken down by *Lactobacillus* species, namely *Lactobacillus plantarum*, *Lactobacillus casei*, and *Lactobacillus fermentum* [20,21]. Gas chromatography-mass spectrometry (GCMS) analysis reveals high SCFA concentration in the *Torani* [22]. In addition to altering phagocytosis and chemotaxis, the SCFAs have been demonstrated to produce reactive oxygen species (ROS) and alter cell proliferation. They also possess antibacterial, anti-inflammatory, and anticancer properties. *Torani*'s microbiota and SCFA concentration may reduce CD colonization and improve the gut microbiome [23,24].

Probiotics and prebiotics have been shown to lessen CD colonization [25,26]. The elderly are particularly at risk for CDI. Therefore, the primary focus for documentation on CD colonization and CDI prevention continues to be hospitals. This study aims to document the effect of a *Torani*-xylitol mixture (i.e., a combination of prebiotics, probiotics, and SCFAs) on the CDI and CD colonization status, along with the safety and tolerability of the elderly population.

## Materials and methods

Study design

This two-arm, open-label, randomized controlled trial (RCT) will be conducted at the Kalinga Institute of Medical Sciences (KIMS), Bhubaneswar, Odisha, India.

Participant and eligibility criteria

The patients aged above 60 years, of any gender, admitted to the hospital within the last 48 hours, anticipated to be admitted for at least seven days, and allowed orally or through the nasogastric tube will be included. The patients with known immunocompromised status (on high-dose steroids or immunosuppressants), scheduled for or who underwent any surgical procedure, on nil-per-oral (NPO) advice, admitted for only diagnostic tests or short-term assessment, requiring life support systems for unstable vitals, with renal failure or on fluid restriction, on any probiotics, with known food allergy or intolerance to xylitol, not complying with the study protocol, and very sick patients (death is thought to be imminent) will be excluded.

Study procedure

Investigational Product

The participants shall consume either of the two products under supervision. The products shall be prepared daily in the kitchen, packaged in similar bottles labeled with the participant ID, and supplied to the participants for daily consumption for up to 14 days.

Intervention Product

The participants in the intervention arm (Group A) shall receive the *Torani*-xylitol mixture containing 350 ml *Torani* (overnight fermented rice water prepared from cooked rice) and 5 gm xylitol once daily for up to 14 days. There is no prohibition on consuming the product with the meals.

Comparison Product

The participants in the comparator arm (Group B) shall be provided 350 ml of plain mineral water.

Randomization and Blinding

After obtaining informed consent, the participants (a total of 200 in the two groups) will be randomized into either of the two groups in a 1:1 ratio, following computerized permuted block randomization with block sizes of 4 and 6 (generated by an independent biostatistician using a web-based random number generator). Allocation concealment will be done using double-layered opaque envelopes. After obtaining consent from the participant, the research staff will inform the independent nurse (who will have the envelopes for randomization) to open the envelope and identify the group allocation, assign the study ID sequentially as per the envelope, and inform the study team member. Once opened for a participant, the envelope will not be used for another participant, even if the participant declines participation subsequently. The used envelopes shall be submitted to the independent statistician.

After opening the sealed envelope and allocating the participant, the study team member will inform the product preparation team (PPT) about the study ID and allocation group for the supply of the study product. The study products shall be prepared daily, packed in similar bottles, labeled with the participant’s ID (neither group nor product mentioned), and supplied individually to the concerned participant’s bedside. The products (i.e., *Torani*-xylitol mixture or plain mineral water) shall be supplied in sealed bottles labeled with the study IDs of the participants to the respective participant’s bedside daily (morning hours). The participants shall be asked to consume these drinks within two hours of supply, and the bottles shall be collected.

Due to the nature of the products, the participants and research staff cannot be blinded. The laboratory analysis and outcome-assessing teams will be blinded to the study group allocation. The bottles shall be selected to minimize the visualization of the product. For any reason, if required, the investigation product may be stopped (temporarily or completely) as per the instruction of the treating doctor.

Data Collection and Follow-Up

The data on sociodemography, anthropometry, clinical information (illness, diagnosis, and comorbidities), and fresh stool samples or rectal swabs will be collected after recruitment. During the intervention and hospital stay, data on clinical progress, investigations (blood, microbiological, radiological), medications and antibiotics, dietary intake, and probiotics/prebiotics use. On day 15, the stool sample or rectal swab will be collected after the investigational product consumption. At discharge/death/referral, the final diagnosis, clinical condition, outcome, medications given, investigation findings, and isolated organisms (any sample source) will be documented. If the patient continues to be hospitalized beyond day 15, an additional stool sample or rectal swab will be collected at the time (within 24 hours) of discharge. During the hospitalization period, a stool sample or rectal swab will be collected for testing if CDI is suspected in any participant (with fever, diarrhea, abdominal pain, or distension). The participants will be followed up (physically/telephonically) on days 30 (+7), 60 (+7), and 90 (+7) post-recruitment to document health status, any illness/infection, medication use, hospitalization, investigations, dietary practices, and probiotic use. The data will be collected using structured case record forms (CRFs).

Adherence and tolerance to the investigational product shall be documented daily during hospitalization. Refusing to participate or withdraw will not affect the participant’s standard care in the hospital. Any untoward medical occurrence, irrespective of the causal relationship, will be recorded and investigated in detail. The serious adverse events (SAEs) shall be evaluated, and causality shall be assigned as unrelated, unlikely, possible, probable, definite, or not assessable.

Outcome Assessment

The CD colonization status will be documented by culture of stool or rectal swabs collected on days 0 and 15. The stool or rectal swab samples will be subjected to glutamate dehydrogenase (GDH) and toxin assay (by enzyme immunoassay, EIA) tests for the participants with suspected CDI. The samples positive for GDH and/or toxin shall be subjected to a nucleic acid amplification test (NAAT). In confirmed cases of CDI, culture for CD (using selective media and anaerobic gas pack) shall be done. The positive culture isolates shall be subjected to VITEK-2 for antimicrobial susceptibility testing (AST). The sample aliquots shall be stored at -80°C for further analysis.

The CD-positive isolates from 30 participants (10 each of those who acquired CD, who eliminated CD, and who had confirmed CDI) shall be subjected to whole genome sequencing. The fecal cytokines (e.g., CXCL-5, CXCL-8) and lactoferrin shall be estimated by enzyme-linked immunosorbent assay (ELISA) kit in a subset of 25 participants per group from stool or rectal swab samples collected on days 0 and 15. The *Torani* product samples will be cultured to detect microbiota (e.g., *Lactobacillus* species), followed by the bacteria species identification (16S rRNA gene amplification) and analysis of SCFAs by high-performance liquid chromatography (HPLC).

Statistical analysis

Sample Size Calculation

A study documented that probiotic consumption reduced CDI by approximately 70% [27]. Assuming that the *Torani*-xylitol mix shall reduce the CD colonization from 15% to 5% in hospitalized participants at discharge, the estimated sample size is 196 participants (98 per group) with a 95% confidence level and 80% power. Thus, we propose to include 200 participants (100 per group).

Data Analysis

The normality of the data distribution will be gauged using the Shapiro-Wilk test. The continuous variables will be expressed as mean and standard deviation or median and interquartile range based on the distribution pattern. The categorical variables will be expressed as frequency and proportion. Missing data will be addressed using various imputation techniques, and sensitivity analyses will be conducted to assess the robustness of the results. The quantitative data with normal distribution will be compared using the unpaired t-test, and those with skewed distribution will be analyzed using the Mann-Whitney U test. The categorical data will be compared using the chi-square or Fisher's exact test, as applicable. Analysis of variance (ANOVA) or the Kruskal-Wallis test shall be considered for the multiple comparisons. A p-value of < 0.05 will be considered significant. For the study outcomes, results will be summarized in absolute (risk difference or mean difference) and relative (risk ratio) effect size measures along with their 95% confidence intervals. Regression analysis shall be done to identify the factors that influence CD colonization or infection and their strength of association. A per-protocol (PP) analysis will be performed to assess efficacy. The safety analysis will be done using the intent-to-treat (ITT) principle. R software (version 4.5.0 or higher) will be used for the data analysis and generation of plots [28].

Interim Analysis

One interim analysis is proposed after enrollment of 50% (n = 100) of participants and completion of the day-15 data. The interim analysis will be conducted using the O’Brien-Fleming spending function and a type I error rate of 5%.

Ethical Consideration and Trial Registration

The Institutional Ethics Committee of KIMS, Bhubaneswar, has approved the study protocol (KIIT/KIMS/IEC/1753/2024). The trial has been prospectively registered with the Clinical Trial Registry of India (CTRI/2025/03/083479). The study will comply with the Good Clinical Practice (GCP), the Declaration of Helsinki, and institutional norms. All the participants will be recruited for the study after obtaining written informed consent, and their privacy and confidentiality will be maintained.

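### Non-compliance is listed as an exclusion with no time point, so randomised non-compliers can be dropped after allocation

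*Protocol article*

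**What the plan says.** All of the text is in the protocol article, Materials and methods.

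- **Eligibility.** Under the heading "Participant and eligibility criteria", the exclusions close with patients "not complying with the study protocol, and very sick patients (death is thought to be imminent) will be excluded". No time is given at which non-compliance is judged.
- **Order of events.** *Randomization and Blinding* places allocation after consent: "After obtaining informed consent, the participants (a total of 200 in the two groups) will be randomized". Product is supplied only after the envelope has been opened.
- **Who knows the allocation.** "Due to the nature of the products, the participants and research staff cannot be blinded". The laboratory and outcome-assessing teams are blinded.
- **Refusal or stopping after allocation.** "Once opened for a participant, the envelope will not be used for another participant, even if the participant declines participation subsequently". Separately, "the investigation product may be stopped (temporarily or completely) as per the instruction of the treating doctor". Neither sentence says how such a participant is treated in the analysis.
- **When compliance is observed.** *Data Collection and Follow-Up*: "Adherence and tolerance to the investigational product shall be documented daily during hospitalization".
- **Analysis sets.** *Data Analysis*: "A per-protocol (PP) analysis will be performed to assess efficacy". The intent-to-treat principle is named for safety only.

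**The concern.** Most items in the exclusion list are states that can be established at the bedside before consent, such as renal failure, current probiotic use or a known intolerance. Non-compliance is a behaviour. A patient has no product to comply with until the envelope is opened. Read literally, this item can be met only after randomisation, and the people placed to apply it know which drink the participant was given.

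Correcting the efficacy population alone would leave the item in place. A participant relabelled as ineligible after allocation could be left out before any analysis set is formed, whatever that set is called. The same applies to safety and tolerability, which the Introduction names as part of the aim: dropping people who stop because they cannot tolerate the drink would remove the observations that the aim needs.

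**Working it through.** **Step 1. The passages side by side.** The item has no time limit. Adherence is recorded daily during the hospital stay, after allocation. Research staff are unblinded. Efficacy is assessed per protocol. No sentence fixes eligibility at randomisation, and none orders removal of a randomised participant. The text therefore permits removal after allocation without requiring it.

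**Step 2. Inputs for the illustration.** The plan gives no figure for non-compliance, so there is none to reproduce. From *Sample Size Calculation*: colonization of 15% and 5%, a planned effect of 15 − 5 = 10 points, and 100 participants per group. Everything else is assumed:

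- no true effect, with 15% colonized in both arms if everyone is kept;
- removal from one arm only;
- f = fraction of that arm removed;
- k = risk in those removed divided by risk in those kept.

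**Step 3. Formula.** If p is the risk in those kept, then (1 − f)p + f·k·p = 0.15, so p = 0.15 / (1 − f + f·k). The spurious difference is 0.15 − p.

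| f | k | 1 − f + f·k | p | Spurious difference |
|---|---|---|---|---|
| any | 1 | 1.00 | 15.0% | 0 points |
| 0.10 | 1.5 | 1.05 | 14.3% | 0.7 points |
| 0.20 | 2 | 1.20 | 12.5% | 2.5 points |
| 0.20 | 3 | 1.40 | 10.7% | 4.3 points |
| 0.30 | 3 | 1.60 | 9.4% | 5.6 points |

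**Step 4. Cross-check with absolute risks.** Let q be the colonization risk in those removed. Then p = (0.15 − f·q) / (1 − f).

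- f = 0.20, q = 25%: (0.15 − 0.05)/0.80 = 12.5%, a difference of 2.5 points. This is the k = 2 row again, since 25/12.5 = 2.
- f = 0.20, q = 35%: (0.15 − 0.07)/0.80 = 10.0%, a difference of 5.0 points.
- f = 0.10, q = 25% to 35%: 13.9% to 12.8%, a difference of 1.1 to 2.2 points.
- f = 0.05, q = 25% to 35%: 14.5% to 14.0%, a difference of 0.5 to 1.1 points.

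**Step 5. Effect on the false-positive rate.** With 100 participants in the intact arm and 100(1 − f) in the other, a two-sided 5% pooled test of two proportions (normal approximation) rejects a true null in:

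- 5.1% to 5.5% of trials at f = 0.05;
- 5.5% to 7.2% at f = 0.10;
- 7.5% to 16.4% at f = 0.20.

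Each range runs from q = 25% to q = 35%. At q = 15% the rate stays at 5.0%.

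**Step 6. Direction.** Removing higher-risk patients from Group A produces a spurious benefit. Removing them from the water arm reverses the sign, and so does removing lower-risk patients from Group A.

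**The case against.** The item stands in an eligibility list, among states judged at screening, in an article that condenses a fuller protocol. The ordinary reading may be a patient unwilling or unable to follow the procedures, and willingness to give samples and accept follow-up can be judged before randomisation. The operational text also leans against removal: the product can be stopped without any mention of leaving the study, non-adherence is recorded, and follow-up to day 90 carries no adherence condition. This stands as a reason to doubt that removal is intended. It does not mend the sentence, which says something else; the point concerns the wording given, not a detail left out.

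A reader might go further and infer that the criterion biases even an intent-to-treat comparison. The documents do not support that. They plan intent-to-treat for safety only, and an analysis that keeps every randomised participant is unaffected. Bias would need the criterion to be applied after allocation and the set to be formed without those removed.

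A reader might also infer that removals would fall mainly in Group A and flatter the intervention. Fermented rice water with xylitol may be harder to take daily than plain water, but no adherence data are given. Supervised intake, the nasogastric route and freedom to take the drink with meals all favour adherence, and the Discussion expects *Torani* to be acceptable.

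Finally, the per-protocol efficacy analysis is already the more direct route to the same bias. That is correct: the illustration does not show bias from this line beyond what per-protocol selection could produce. The line still matters because it would survive a correction of the analysis population and could also reach safety.

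**Conclusion.** The point holds as a defect of wording with a conditional consequence. As written, the exclusion can be applied after allocation by staff who know the group, and with the per-protocol efficacy analysis it leaves room for randomised non-compliers to be dropped. It can bias efficacy, safety and tolerability comparisons only if removal differs by arm and those removed differ in risk.

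The colonization figures range from negligible, when few are removed or their risk is close to average, to a quarter or more of the planned effect when 20% are removed at double the risk or higher (2.5/10 = 25%; 4.3/10 = 43%). The fractions removed, the risk ratios and removal from a single arm are all assumptions. No size is estimated for safety or tolerability. The sign of any bias is open.

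**What to change.** Before recruitment starts:

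1. Replace the item with a judgement made before randomisation, for example: 'unwilling, or judged before randomisation to be unable, to follow the study procedures'.
2. State that eligibility is fixed at randomisation and that later non-adherence is not a reason for exclusion.
3. State that non-adherent participants continue to be sampled and followed.
4. Analyse them in their allocated group for efficacy as well as safety, with the per-protocol analysis as supportive.

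This takes a line or two of text in the eligibility and analysis sections, and the planned number of participants need not change on this account. The price is possibly some dilution of the observed effect, because people who took little of the product stay in their group. The article says the study has not commenced, so the change can still be made cleanly; participants dropped and left unsampled could not be recovered later.

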## Discussion

This RCT has been designed to document the effect of the *Torani*-xylitol mixture on CD colonization and CDI by modulating gut microbiota among hospitalized elderly patients. The outcome measures are CD colonization, CDI incidence, CD profile (genotype, phenotype, and AST) of CD, and safety of the investigational product. As gut dysbiosis is an important causative factor for CDI, the probiotic-prebiotic-synbiotic products have potential roles [11,14]. The traditional probiotic-rich foods like *Torani* (fermented rice water) in Odisha provide advantages in their acceptability, ease of preparation, availability and use, and affordability. The components of *Torani*, like SCFA and enrichment with prebiotic (xylitol), are likely to repair gut dysbiosis, modulate colonic milieu, improve gut immunity, and prevent CD colonization and CDI [14,15,17,19].

This study has a few limitations. First, the study design is an open-label RCT, owing to the nature of the intervention. Allocation concealment will be done to mitigate the performance and detection bias. Second, the duration of therapy is fixed for all participants irrespective of the group, gender, disease, or hospitalization duration. Third, we could not get the exact power analysis for this study, as this is the first study to document the effect of the *Torani*-xylitol mixture on CD colonization and CDI.

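### The colonisation endpoint is stated with three different time points, and the Methods name no sample for patients who leave before day 15

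*Protocol article*

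**What the plan says.** The protocol article places the post-baseline colonisation measurement at three different times.

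- **Outcome Assessment:** "The CD colonization status will be documented by culture of stool or rectal swabs collected on days 0 and 15".
- **Sample Size Calculation:** the mixture "shall reduce the CD colonization from 15% to 5% in hospitalized participants at discharge".
- **Abstract, Methods:** "Stool samples or rectal swabs will be collected on days 0 and 15 or at discharge/death/referral for CD isolation".

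Data Collection and Follow-Up sets the sampling schedule. It has a sample at recruitment and one on day 15, and then: "If the patient continues to be hospitalized beyond day 15, an additional stool sample or rectal swab will be collected" within 24 hours of discharge. For discharge, death or referral in general it lists information to be recorded (diagnosis, condition, outcome, medications, findings, organisms already isolated) and no study sample. Samples for suspected infection are taken in hospital and only when symptoms prompt them. The contacts on days 30, 60 and 90 may be by telephone, and no stool or swab is listed for them.

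Eligibility asks only that the patient be "anticipated to be admitted for at least seven days".

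**The concern.** Colonisation is the outcome on which the trial is sized, and the Discussion lists it first among the outcome measures. For a patient who leaves in the second week, or who stays well past day 15, the three statements point to different samples, and one of them may never be taken.

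Two things are at stake. First, a swab that was not collected cannot be recovered by any later analysis plan, so the sampling rule has to be right in the protocol. Second, leaving before day 15 is a post-randomisation event that is likely to be related to prognosis. Comparing only those with a day-15 sample could therefore distort the comparison between arms as well as shrink it.

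**Working it through.** **Step 1. Apply each section to two patients.** One is discharged on day 9, the other on day 25. Eligibility allows both.

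| Section | Leaves on day 9 | Leaves on day 25 |
|---|---|---|
| Abstract | sample at discharge | day 15 or discharge |
| Data Collection and Follow-Up | none named at discharge; no collection described once the patient has left | day 15, plus an additional sample at discharge |
| Outcome Assessment | day 15, after the patient has gone | day 15 |
| Sample Size Calculation | status on day 9 | status on day 25 |

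For the early leaver, only the Abstract supplies the sample that the sample size assumption needs. For the long stayer, Outcome Assessment points to day 15 and the sample size sentence to discharge.

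**Step 2. The plan's own figure.** Inputs from Sample Size Calculation: p1 = 0.15, p2 = 0.05, 80% power, 95% confidence (sidedness not stated), 98 per group, rounded up to 100. With the usual pooled formula, two-sided 5%:

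n = [1.96·√(2·0.10·0.90) + 0.8416·√(0.15·0.85 + 0.05·0.95)]² / 0.10²

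= [0.8316 + 0.8416·0.4183]² / 0.01 ≈ 140.1, so 141 per group.

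The stated 98 is not reproduced. The only match found is 15% versus 4.5% with a one-sided 5% test, and those are not the stated rates. This is a separate problem. It matters here only because it sets the baseline power from which any loss from missing samples must be counted.

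**Step 3. Power with fewer evaluable patients.** z = (0.10·√n − 0.8316) / 0.4183, and power = Φ(z).

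- n = 100: (1.0000 − 0.8316)/0.4183 = 0.403, power about 66%.
- n = 70: (0.8367 − 0.8316)/0.4183 = 0.012, power about 50%.
- n = 40: (0.6325 − 0.8316)/0.4183 = −0.476, power about 32%.

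The article does not give the share who leave before day 15 without a sample, so the range below is assumed, with the same share in both groups:

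| Assumed share without a sample | Evaluable per group | Power, 15% v 5% |
|---|---|---|
| 0% | 100 | 66% |
| 10% | 90 | 61% |
| 20% | 80 | 56% |
| 30% | 70 | 50% |
| 40% | 60 | 45% |
| 50% | 50 | 38% |
| 60% | 40 | 32% |

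The loss due to this point is the drop from the first row. At 30% it is about 16 percentage points (66 − 50).

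**The case against.** The strongest reply is that the Abstract is part of the document and already covers early discharge. That is correct. A reader might infer that, as the plan stands, the endpoint will be missing for everyone who leaves early. The text does not support this: the Abstract provides for that sample, the day-15 sentence in Data Collection is not expressly limited to inpatients, and the flow diagram is not available to check. If sites follow the Abstract, the loss could be close to zero. What stands is the contradiction, because the detailed sections that staff would work from do not repeat the Abstract's rule.

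Four other strong readings also go too far.

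- *No rule exists for long stays.* Outcome Assessment names day 15, Data Collection calls the later swab additional, and the interim analysis waits for day-15 data. Only the sample size phrase "in hospitalized participants at discharge" conflicts.
- *Early leavers are the healthier patients, so the bias has a known direction.* They also include patients who die or are referred. The direction is unknown.
- *Early discharge takes power from 80% to 50%.* The fall from 80% to about 66% comes from the sample size error, not from this point.
- *The exposure wording is part of the same defect.* The product is given "once daily for up to 14 days", while the Discussion says "the duration of therapy is fixed for all participants irrespective of the group, gender, disease, or hospitalization duration". Both can describe one standard planned course for all. The wording could be made clearer, but it does not bear on when colonisation is measured.

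Data Analysis also promises imputation and sensitivity analyses. These soften the consequence of some missing samples, but they neither define the endpoint nor replace a sample that the schedule never asked for.

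**Conclusion.** The point holds as an internal inconsistency with a practical consequence. The article gives three time points for colonisation, and its Methods name no post-baseline colonisation sample for a patient who leaves before day 15. Since seven anticipated days suffice for entry, such departures are foreseeable.

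The size depends on a share that the documents do not give. At an assumed 30% without a sample, power falls from about 66% to about 50%; at an assumed 60%, to about 32%. These figures rest on a two-sided 5% test, the stated 15% and 5% rates, equal loss in both groups and no imputation. They describe what happens if the Methods are followed instead of the Abstract. They do not forecast the trial's actual loss. Any bias from selective loss comes on top, and its direction cannot be stated.

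**What to change.** The article says the study has not started, so this can be settled before recruitment.

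1. In Data Collection and Follow-Up and in Outcome Assessment, carry over the Abstract's rule: one endpoint sample per participant, taken on day 15, or at discharge, referral or death if that comes earlier.
2. State that for stays beyond day 15 the day-15 sample is the endpoint and the additional discharge sample is secondary.
3. Reword the sample size sentence so that 15% and 5% refer to that same endpoint.
4. Report the day of sampling by arm, and add a sensitivity analysis for its variation.

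The cost is a change of wording plus one swab at early departure, which the Abstract already foresees. The drawback is that the timing of the endpoint then varies with length of stay, which may itself differ between arms; step 4 is there for that reason. Sampling everyone on day 15, including those already discharged, would also reconcile the text and would fix the timing, but it needs a collection after discharge that the article does not now describe.
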